### T2DM-related skin variables

- Sudomotor function (in each hand or foot, average in hands, average in feet, overall average)
- Skin hydration

### Exploratory skin variables

- Epidermal barrier function
- Epidermal barrier recovery
- Epidermal barrier integrity
- Skin thickness
- WH
- RNA-seq gene expression profiling

### Other secondary variables

- 24 hour urinary free cortisol

### Feasibility

- Data on eligibility (proportion of patients assessed for eligibility deemed to be eligible and for each inclusion/exclusion criterion, proportion of patients eligible)
- Data on recruitment success (recruitment rate per month and week by week)
- Data on consent success (proportion of eligible patients consented)

- Assessment of randomization (evenness of numbers randomised to the two groups and balance of baseline characteristics between the two groups)
- Data on adherence to intervention (number of patients completing diary card, percentage compliance throughout treatment phase and reasons for missed doses)
- Data on retention to trial (number of patients completing final study assessment, reasons for discontinuation and number discontinuing in each case)
- Data on completeness of outcome measure reporting (for each outcome, number of patients with data available at each visit)

## 5. STUDY DESIGN

### 5.1. Study description

This study aims to conduct a double-blind, randomised, parallel group, placebo-controlled phase II pilot trial of 35 days' duration with 400mg oral AZD4017 twice daily (n=15) or placebo (n=15) in patients with T2DM.

Eligible participants will be identified using medical records from the Diabetes Clinic at St. James' University Hospital (SJUH) by the CI or an authorised member of the direct care team. Once identified, patients will be invited to participate in the trial by email and/or post and provided with a Participant Information Leaflet (PIL) and PIL Feedback Form (returnable by self-addressed prepaid envelope).

Patients will be contacted by telephone to confirm willingness to participate and eligibility after 72 hours since sending the PIL.

### 5.2. Study duration

The protocol treatment duration is 35 days with follow-up visit at least 7 days after the last treatment dose.

Skin, plasma, serum and 24 hour urine samples will be stored for future biochemical analyses but storage will not exceed 5 years after the end of the trial. At 5 years after the end of the trial any residual samples will either be destroyed or placed in an approved Research Tissue Bank.

### 5.3. Rationale for study design and selection of dose

#### AZD4017 efficacy

The ability of 11 $\beta$ -HSD1 inhibitors to reduce 11 $\beta$ -HSD1 activity in peripheral tissues has not been determined in man. Our primary variable will therefore evaluate the ability of AZD4017 to inhibit 24 hour 11 $\beta$ -HSD1 activity in skin. In addition to assessment of efficacy, this outcome measure will be used to provide preliminary data on associations between 11 $\beta$ -HSD1 activity levels and skin function variables. To support this outcome measure,

secondary variables will include systemic AZD4017 efficacy by measuring urinary cortisol to cortisone metabolite ratios ([THF+alloTHF]/THE) and pharmacokinetic analyses to confirm AZD4017 levels in plasma and skin biopsies.

### **Safety**

AZD4017 has been studied in healthy human volunteers and is tolerated when given in single doses up to 1500mg and in multiple doses up to 900mg for periods of up to 9 days. A Phase IIa study of 28 days duration has been conducted in patients with raised intraocular pressure; 7 subjects received 200 mg once daily AZD4017 for up to 28 days and 19 subjects received 400 mg twice daily AZD4017 for up to 28 days. The most commonly reported AE in the studies with AZD4017 were gastrointestinal disorders and headache and were of mild to moderate intensity. Previous safety studies in healthy volunteers also reported an increase in ACTH and dehydroepiandrosterone sulfate levels. However, cortisol and testosterone levels were not changed. As the proposed pilot trial is relatively short, we will measure dehydroepiandrosterone sulfate and testosterone. However, blood samples will be stored allowing ACTH and cortisol to be measured in any patient showing evidence of hypothalamic-pituitary-adrenal (HPA) axis activation.

Other safety laboratory analyses showed no clinically relevant changes. No clinically relevant changes or trends were seen in vital signs or in ECG results in previous safety studies.

Although other 11 $\beta$ -HSD1 inhibitors have been trialled in patients with T2DM and were safe and well-tolerated [32, 33], AZD4017 has not been tested in this patient cohort. This preliminary pilot trial will therefore evaluate safety by monitoring validated safety variables of T2DM (e.g. BMI, waist-hip ratio, BP, HbA1c and lipids) and AZD4017 (e.g. FBC, LFT, eGFR, U+E, adrenal and thyroid function). Further information regarding non-clinical data and previous clinical studies can be found in the AZD4017 IB.

Data collected will be used to inform powering and feasibility of a future confirmatory trial.

### **Treatment duration**

The study design is suitable for the time and funding constraints available. The study duration (35 days) is sufficient to detect changes in all T2DM-related skin secondary outcome measures [35-39].

### **Dose**

AZD4017 is a novel orally bioavailable small molecule inhibitor of 11 $\beta$ -HSD1 enzyme activity. It is potent and highly selective *in vitro* and *in vivo*. The half maximal inhibitory concentration (IC50) for inhibition of 11 $\beta$ -HSD1 activity (cortisone to cortisol conversion) is 2nM. AZD4017 is selective (> 2000x) for 11 $\beta$ -HSD1 over human recombinant 11 $\beta$ -HSD2 and the closely-homologous enzymes 17 $\beta$ -hydroxysteroid dehydrogenase 1 (17 $\beta$ -HSD1) and 17 $\beta$ -hydroxysteroid dehydrogenase 3 (17 $\beta$ -HSD3) *in vitro*.

The dose to be used in this study is 400mg twice daily. This dose results in a decrease in the urinary ratio of tetrahydrocortisol to tetrahydrocortisone metabolites ([THF+alloTHF]/THE) from 0.99+0.27 to 0.11+0.06 and decreases the generation of plasma prednisolone following oral prednisone by 80%. Pharmacokinetic and pharmacodynamic data from single and multiple ascending dose studies in healthy volunteers suggest that a dose of 400mg twice daily may achieve approximately 90% inhibition of 11 $\beta$ -HSD1 over 24 hours. The safety and tolerability profile of AZD4017 has been studied in animals and in single and multiple ascending dose studies in human volunteers and supports the use of AZD4017 twice daily to 900 mg/day. The 35-day treatment period is considered sufficient to see sustained inhibition of 11 $\beta$ -HSD1 by AZD4017, and therefore this dose and duration is appropriate. Please refer to IB for more information.

### **Other secondary variables**

Additional secondary study variables have been selected to represent a combination of clinically validated disease-related and/or GC-regulated exploratory outcome measures of skin function. Peripheral diabetic neuropathy in diabetes is characterized by a decrease in intra-epidermal nerve fiber density and sudomotor function leading to decreased skin hydration which and an increased risk of DFU [40-47]. Sudomotor function analysis has superseded intra-epidermal nerve fiber density as the “gold standard” for evaluating peripheral diabetic neuropathy and measures sweat gland innervation as a direct indicator of cutaneous C-fiber function [48]. Although the regulation of sudomotor function by GC is poorly understood, skin hydration is known to be reduced by GC treatment [49] and will also be investigated as a secondary study variable. The proposed study will generate novel data on the regulation of DFU risk factors by 11 $\beta$ -HSD1-mediated GC activation in skin.

Previous studies have indicated increased TEWL following treatment with topical GC [50] and acute systemic stress [51]. Conversely, acute systemic stress (physical restraint) decreased TEWL in rodent models of inflammatory diseases [52]. Therefore, we anticipate that limiting local GC reactivation by 11 $\beta$ -HSD1 inhibition may regulate TEWL. Impaired barrier recovery has been reported following systemic GC excess in humans [53] and rodents [54-56]. The number of tapes required to induce a standardized degree of barrier disruption will be used to evaluate barrier integrity, which is also impaired by GC excess [55, 56]. Skin thinning is a frequently reported side-effect of GC excess driven by both dermal and epidermal thinning [8, 9, 12, 57, 58], however, regulation of skin thinning by 11 $\beta$ -HSD1 in man remains unexplored. Impaired WH is a common side-effect of GC excess [11, 59] and 11 $\beta$ -HSD1 has been implicated in mouse WH models by us [19, 22] and others [23, 24]. However, this remains to be investigated in man. Although chronic wounds are a widely reported feature of T2DM, acute WH has not been fully investigated. Moreover, TEWL, barrier recovery, epidermal integrity and skin thickness remain unexplored in T2DM. Our study will provide a new insight into the regulation of these key skin functions by 11 $\beta$ -HSD1 in T2DM. RNA-seq will also be used for transcriptomic profiling of gene expression to identify key pathways involved in 11 $\beta$ -HSD1-mediated regulation of skin function.

Systemic GC levels have been shown to be important in determining peripheral GC exposure by regulating 11 $\beta$ -HSD1 substrate (cortisone) availability [18]. Therefore, systemic GC levels in combination with peripheral 11 $\beta$ -HSD1 activity may affect AZD4017 responsiveness and will also be monitored by measuring 24 hour urinary free cortisol levels.

Study feasibility will be assessed using a range of quantifiable measures including eligibility, recruitment, consent, randomization, adherence, retention and data completeness as in accordance with Consolidated Standards of Reporting Trials guidance [60, 61].

## **6. SELECTION AND WITHDRAWAL OF SUBJECTS**

### **6.1. Target population**

Adults aged 18 years or older, with T2DM

### **6.2. Estimated number of eligible participants**

Current data from the NIHR Yorkshire and Humber Clinical Research Network identified >45,000 patients with T2DM from 11 general practitioner (GP) practices, indicating a large target population pool. Therefore, we estimate a trial invitation requirement of 86 participants of whom an estimated 50% will consent and of whom an estimated 70% will be eligible (using the criteria below) to reach our target of 30 participants (allowing a 20% post-randomization drop-out rate to achieve a total of 24 completers with 12 in each arm).

### **6.3. Eligibility criteria**

#### **6.3.1. Inclusion criteria**

- 1) Able and willing to provide informed consent
- 2) Clinical diagnosis of T2DM with HbA1c <11% (<97 mmol/mol) at screening while taking standard therapy at a stable dose for  $\geq 10$  weeks

#### **6.3.2. Exclusion criteria**

- 1) Women of child-bearing potential (WOCBP). Note: WOCBP include any female who has experienced menarche and who has not undergone successful surgical sterilization (hysterectomy, bilateral tubal ligation, or bilateral oophorectomy) or is not postmenopausal [defined as amenorrhea  $\geq 12$  consecutive months or women on hormone replacement therapy with documented serum follicle stimulating hormone level >35 mIU/mL].

Additionally, male study participants who are sexually active with a female partner of childbearing potential must be surgically sterilized or agree, along with their partner, to use a highly effective method of birth control (as defined below) from the time of screening until 3 weeks after final dose of study drug (5 drug elimination half-lives plus 2 weeks). Male

study participants must also **not** donate sperm from the time of screening until 3 weeks after final dose of study drug (5 drug elimination half-lives plus 2 weeks).

Highly effective methods of contraception are defined as combined (estrogen and progestogen containing) hormonal contraception associated with inhibition of ovulation (either oral, intravaginal or transdermal), progestogen-only hormonal contraception associated with inhibition of ovulation (either oral [such as Cerazette™], injectable or implantable), intrauterine device (IUD), intrauterine hormone-releasing system (IUS), bilateral tubal occlusion, vasectomized partner or true sexual abstinence: When this is in line with the preferred and usual lifestyle of the subject. [Periodic abstinence (e.g., calendar, ovulation, symptothermal, post-ovulation methods), declaration of abstinence for the duration of a trial, and withdrawal are not acceptable methods of contraception].

2) Active leg/foot ulceration

3) Acute electrocardiogram (ECG) anomalies deemed to be clinically relevant by the CI

4) Systemic hypertension (BP >150/90), on 3 successive measurements at the screening visit (patients with controlled hypertension can be included in the trial) with the first acceptable measurement recorded and either systolic or diastolic BP exceeding these values requiring re-measurement

5) Any endocrine disorder (other than T2DM), including type 1 or secondary diabetes, except treated hypothyroidism with normal thyroid function tests for at least 3 months

6) Suspicion of or known Gilbert's disease

7) Alanine aminotransferase (ALT) and/or aspartate aminotransferase (AST) and/or alkaline phosphatase (ALP) > 1.5x upper limit of normal (ULN)

8) Bilirubin (total) > 1.5x ULN

9) An eGFR calculated by the Modification of Diet in Renal Disease equation of <45 ml/min/m^2

10) Creatine kinase (CK) >2 x ULN

11) Participant is, at the time of signing the informed consent, a user of recreational or illicit drugs (including marijuana) or has had a recent history (within the last year) of drug or alcohol abuse or dependence on questioning or clinical history

12) Receiving any topical, systemic (including vaginal/rectal) or inhaled GC treatment at the time of or within 3 months prior to the screening visit

13) Taking any anticoagulant medication (blood thinning e.g. warfarin)

14) Taking probenecid or similar (for gout) at the time of inquiry

15) Any medical/surgical procedure (excluding skin biopsies) or trauma during IMP administration or within one week following the last administration of the IMP as judged by the CI

16) Involved in the planning and/or conduct of the study (applies to both AstraZeneca staff and/or staff at the study site)

17) Participated in any other clinical study within 1 calendar month prior to the screening visit (except registry-only participation)

18) Deemed otherwise inappropriate to participate by the trial team

### **6.3.3. Exclusions for general safety**

Not applicable

### **6.3.4. Screen failures**

Participants who sign an Informed Consent Form and fail to meet the inclusion and/or exclusion criteria are defined as screen failures. For all screen failures, the investigator is to maintain a Screening Log that documents the screening number, participant initials, and reason(s) for screen failure. A copy of the log will be retained with the Case Report Form (CRF) and screening will be recorded as pass or fail in the CRF. Screening Log originals will be stored in the TMF.

## **6.4. Recruitment, consent and randomization processes**

### **6.4.1. Recruitment**

Eligible participants will be identified using medical records from the Diabetes Clinic at St. James's University Hospital by the Chief Investigator or an authorized member of the direct care team. Potentially eligible participants will be selected using a computerized search and review of medical records.

A PIL and PIL Feedback Form will be provided by a qualified member of staff who has signed/dated the staff delegation log for suitable candidates to consider. This will include detailed information about the rationale, design and personal implications of the study. Following information provision, patients will be contacted by telephone after 72 hours to ask whether they would be willing to take part in the trial and to check eligibility. This process will be clearly documented into the patient's medical notes.

### **6.4.2. Consent**

Assenting patients will then be invited to attend a screening visit where they will be formally assessed for eligibility and asked to provide written, informed consent. Where English is not the patient's first language every effort will be made to provide a Trust interpreter according to normal Trust procedures. The right of the patient to refuse consent without giving reasons will be respected. The original Informed Consent Form will be filed in the Trial Master File (TMF), with one copy given to the patient and one filed in the hospital notes. Consent pass or fail will also be recorded in the CRF. The written consent will be taken by an

eligible member of staff who has signed/dated the staff delegation log. The process of obtaining written consent will be clearly documented in the patient's medical notes.

A separate Informed Consent Form will be attained prior to the skin biopsy procedure which will be stored with the general Informed Consent Form in the TMF and recorded as pass or fail in the CRF.

#### **6.4.3. Randomization process**

Treatment groups will be allocated on a fully randomised basis. A randomization schedule will be generated by the dedicated trials pharmacy representative who has signed/dated the staff delegation log and is not otherwise associated with this study. Patients will be randomised in a 1:1 treatment allocation ratio to either AZD4017 or placebo. The randomization schedule will be stored in a password protected file accessible only to the dedicated trials pharmacy (the CI and Scientific Lead will be blinded to the randomization process) until all samples have been collected.

#### **6.4.4. Definition for the end of the trial**

The end of the trial will be defined as entry of the last participant's last data item.

#### **6.5. Withdrawal criteria**

Participants are at any time free to withdraw from study (IMP and assessments), without prejudice to further treatment (withdrawal of consent) at any point. Such participants will always be asked about the reason(s) and the presence of any AE. Participants are not under obligation to give a reason for withdrawal. If possible, they will be invited to attend a follow-up visit, ideally, at least 7 days after stopping the IMP. They will undergo the follow-up visit safety measurements and be formally discharged by telephone. Any AE will be followed up wherever possible and all remaining IMP should be returned by the participant.

Should the participant need to be withdrawn from the active treatment phase of the study between study visits for safety reasons e.g. serious adverse event (SAE) or laboratory abnormalities, study medication will be stopped immediately. If withdrawn from IMP, participants will be free to complete the remaining protocol if they choose to do so unless deemed clinically unfit by the CI, in which case they will be withdrawn from the remainder of the protocol.

IMP withdrawal criteria are as follows:

- 1) Participant decision. The subject is at any time free to discontinue treatment, without prejudice to further treatment
- 2) The participant has a clinically significant or serious AE that would not be consistent with treatment continuation, as determined by the CI or the participant; including but not limited to hospitalisation or disability, requirement for medical or surgical intervention to prevent

hospitalisation or disability; or abnormalities of liver, muscle or thyroid function that are considered unacceptable by the CI

3) Hepatotoxicity: ALT and/or ALP and/or AST >2.5x ULN or bilirubin >2x ULN. This is in keeping with Common Terminology Criteria for AE (v5.0) Grade 2 recommendations from the National Institute of Health.

4) Renal toxicity: eGFR <45

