#### 9.2.2.5. Blood tests

Blood samples collected at screening, baseline, study Visits 3 (day 7), 4 (day 28), 6 (day 35) and follow-up (day 42 onwards) will be analysed immediately through the Leeds Teaching Hospitals NHS Trust Pathology Service or processed and stored for future research.

Blood samples at each of these visits will evaluate HbA1c (mmol/mol) and lipids [total and high density lipoprotein cholesterol and triglycerides (mmol/l)] for T2DM disease markers and FBC [haemoglobin (g/l), white cells and platelets ( $\times 10^9/\text{l}$ ), red cells ( $\times 10^{12}/\text{l}$ ), mean corpuscular volume (fl), haematocrit (%/100), mean corpuscular haemoglobin (pg), mean corpuscular hemoglobin concentration (g/l) and red blood cell distribution width (%)], LFT

[ALT, AST and gamma-glutamyl transpeptidase (iu/l), ALP (U/l), albumin (g/l) and bilirubin (umol/l)], eGFR (ml/min/1.73m^2), U+E [sodium, potassium and urea (mmol/l) and creatinine (umol/l)], adrenal [testosterone (nmol/l) and dehydroepiandrosterone sulphate (umol/l)] and thyroid [thyroid stimulating hormone (mIU/l) and free thyroxine (pmol/l)] function (AZD4017 safety markers). CK (iu/l) will also be measured at the screening visit. Samples will be collected by authorised research nurses.

Results will be sent to the CI or authorised delegated personnel for immediate monitoring signature and dating. Signed and dated result reports will be stored with the patient's medical notes for each visit and recorded in the CRF as pass or fail.

Blood will also be taken at baseline and day 35 for separation to serum and plasma and stored at -80°C in the WTBB designated storage area for plasma AZD4017 detection and future studies (up to 5 years). At 5 years after the end of the trial any residual samples will either be destroyed or placed in an approved Research Tissue Bank.

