| Randomization                      |                      | X           |             |             |              |              |              |                 |
| Tablet supply                      |                      | X           |             |             | X            |              |              |                 |
| 11 $\beta$ -HSD1 activity (biopsy) |                      | X           |             |             | X            |              |              |                 |
| RNA-seq                            |                      | X           |             |             | X            |              |              |                 |

|                                        |  |   |   |   |   |   |   |   |
|----------------------------------------|--|---|---|---|---|---|---|---|
| (biopsy)                               |  |   |   |   |   |   |   |   |
| Skin thickness                         |  | X |   |   |   |   | X |   |
| AE monitoring                          |  |   | X | X | X | X | X | X |
| Evaluation of biopsy site              |  |   | X | X | X | X | X | X |
| Wound healing                          |  |   | X | X |   | X | X |   |
| Compliance monitoring                  |  |   | X | X | X | X | X |   |
| AZD4017 in plasma and skin (biopsy)*** |  |   |   |   |   |   | X |   |

\* Informed consent will also be obtained prior to each biopsy

\*\* HbA1c, lipids, FBC, LFT, eGFR, U+E, adrenal and thyroid function (CK will also be analysed at screening). For further detail see section 9.2.2.5

\*\*\* Active (AZD4017) arm only after unblinding at the end of the trial

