#### **Blood**

A maximum of 70 ml of blood will be collected at each study visit. The blood will be drawn into a combination of tubes, according to the planned experiments. After collection, blood samples will be analysed immediately or processed for serum and plasma and stored at -80°C in freezers at the WTBB SJUH for future biomarker and pharmacokinetic analyses, respectively.

Sample labels containing appropriate identification information will be provided.

The blood measurements to be collected in this study include T2DM-specific (HbA1c and lipids) and AZD4017-related (FBC, LFT, eGFR, U+E, thyroid and adrenal function) safety measures as presented in Table 2.

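### Muscle abnormality is a named reason to stop study drug, but CK is scheduled only at screening, so an isolated, symptom-free CK rise on treatment could go unseen (minor)

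*Protocol*

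**What the plan says.** Protocol section 6.5, criterion 2, allows study drug to be stopped for an adverse event that makes continuing inappropriate. Its open-ended list of examples includes "abnormalities of liver, muscle or thyroid function that are considered unacceptable by the CI". Criterion 3 then sets a numeric liver stop ("Hepatotoxicity: ALT and/or ALP and/or AST >2.5x ULN or bilirubin >2x ULN"), and criterion 4 sets a renal stop at eGFR below 45. Muscle has no numeric stop.

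Exclusion 10 in section 6.3.2 bars entry for "Creatine kinase (CK) >2 x ULN".

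The timing of CK is stated consistently. Section 9.2.2.5 says "CK (iu/l) will also be measured at the screening visit", the Table 1 footnote says "adrenal and thyroid function (CK will also be analysed at screening", and Table 2 agrees. CK is absent from the blood panels listed for Visits 1, 3, 4, 6 and follow-up (sections 10.3, 10.5, 10.6, 10.8 and 10.9), from the monitoring list in section 8.6, and from the safety variables in sections 4.2 and 13.4.2.2.

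The repeated liver panel in section 9.2.2.5 holds "ALT, AST and gamma-glutamyl transpeptidase (iu/l), ALP (U/l), albumin (g/l) and bilirubin (umol/l". The same draws also cover U+E, eGFR and thyroid function. Section 9.2.2.5 adds "Blood will also be taken at baseline and day 35 for separation to serum and plasma", and section 11.10 describes the stored serum and plasma as kept "for future biomarker and pharmacokinetic analyses, respectively".

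**The concern.** The protocol treats muscle as a safety domain in two places: CK is checked as a condition of entry, and muscle abnormality is a named example of a reason to stop drug. Between those two points it schedules no muscle-specific test. The other two organs in the same clause, liver and thyroid, are each followed by blood test through dosing and at follow-up.

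The patient at stake is one whose CK rises on treatment above the level that would have barred entry, without symptoms and without a marked AST rise. That patient could finish dosing with the CI unaware. The planned safety tables would then hold no on-treatment CK unless stored serum were assayed later. An analysis plan cannot repair this, because it cannot summarise a test that was never run.

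Safety is a stated secondary objective, and section 5.3 says that AZD4017 has not been tested in type 2 diabetes. The 35-day course is 35 − 28 = 7 days longer than the longest exposure cited there.

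**Working it through.** The protocol gives no figure of its own on this point, so the check sets the stopping criterion beside the assessment schedule.

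**Scheduled checks after the first dose** (sections 9.2.2.5, 10.4 to 10.9 and 11.6.1; Tables 1 and 2)

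| Check | When | Count |
|---|---|---|
| CK | none | 0 |
| Liver panel (includes ALT, AST, GGT, ALP, bilirubin) | days 7, 28, 35, follow-up | 4 |
| Thyroid function | days 7, 28, 35, follow-up | 4 |
| U+E and eGFR (timing from section 9.2.2.5 and the tables) | days 7, 28, 35, follow-up | 4 |
| Adverse event enquiry | days 2, 7, 28, 30, 35, follow-up | 6 |
| Banked serum | day 35, against baseline | 1, not read in real time |

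Of the four post-dose blood draws, those at days 7 and 28 could still change dosing. Day 35 is the end of dosing, so that draw and follow-up complete the safety record.

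**Gap since the last scheduled CK.** Screening falls on day −7 to −2 and dosing ends on day 35. The interval is 35 + 2 = 37 to 35 + 7 = 42 days.

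**Active-arm exposure without a scheduled CK.** Section 13.9 randomises 15 per arm and allows 20% drop-out, leaving 15 × 0.8 = 12 completers.
- Completers only: 12 × 35 = 420 patient-days.
- All 15 with no drop-out: 15 × 35 = 525 patient-days.

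**Earlier liver enzyme results at 400 mg twice daily** (section 8.6, 19 subjects)
- AST 1 to 1.5 × ULN: 4/19 = 21%.
- ALT 1 to 1.5 × ULN: 3/19 = 16%.
- GGT above ULN: 2 at 1 to 1.5 × and 1 at 1.5 to 2 ×, so 3/19 = 16%.

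These are group counts. They do not show which subjects overlapped, and the protocol does not attribute any of the rises to muscle. None of the AST values reached the 2.5 × ULN stop.

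**Reading the two sides together.** Criterion 2 can be met through symptoms, examination findings or an unscheduled CK, so it can operate without a scheduled one. What no test designated for muscle would reveal is a CK rise with no symptoms and no marked AST change. The protocol would count such a rise: section 11.1 includes abnormal laboratory findings among adverse events, and section 6.5 gives laboratory abnormalities as an example of a safety reason for stopping drug between visits.

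**The case against.** The strongest case for leaving the schedule alone has four parts.

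- **The criterion creates no CK trigger.** Muscle is one discretionary example. The protocol sets numeric laboratory stops where it wants them, for liver and kidney. A CK rise with no symptoms and no marked AST change is the muscle event least likely to matter clinically. This stands, and it keeps the point minor.
- **An entry limit does not oblige later testing.** ECG also has an entry criterion and no on-treatment assessment. That is fair for exclusion 10 alone. It does not answer the separate fact that muscle is named in the stopping criterion.
- **There is other cover.** Clinical evaluation takes place at every visit. AST could flag marked muscle injury, although section 6.5 labels that stop as hepatotoxicity. U+E and eGFR could show serious consequences of muscle breakdown. All of this stands as partial cover. None of it is specific to muscle, and an unscheduled CK is possible but not required.
- **There is no known signal.** Section 8.6 reports no evident muscle effect and refers to the investigator brochure, which is not at hand. Earlier CK data there might justify testing at screening only. This stands.

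A reader might also infer that no scheduled result could help separate a liver from a muscle source of an AST rise. The documents do not support that: GGT, ALP and bilirubin are in the same repeat panel, and GGT rises were reported in the same earlier dose group. CK would only add a direct muscle marker.

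**Conclusion.** The mismatch is real and minor. After the first dose CK is scheduled 0 times, while liver and thyroid, from the same clause, are each scheduled 4 times. An isolated, symptom-free CK rise on treatment could go unseen in real time.

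Two stronger readings should be resisted. The protocol does not contradict itself: all three statements of CK timing agree, and a discretionary criterion can be applied without a scheduled test. Nor do the 420 to 525 patient-days measure risk. They are simply the planned active-arm exposure, and the documents give no rate of CK elevation from which to estimate missed cases.

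The conclusion assumes that CK is the only muscle-specific test intended, as the listed panels indicate, and that nothing in the investigator brochure settles the matter either way. It supports a low-cost precaution in a first use in this patient group. It is not a response to an observed harm.

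**What to change.** Add CK to the blood already drawn at days 7, 28 and 35 and at follow-up. Use the screening value as baseline, which fits the rule in section 13.3 that the last valid pre-dose measurement serves. List CK in sections 4.2, 8.6, 9.2.2.5 and 13.4.2.2 and in Tables 1 and 2. Send results to the CI by the review route already in section 9.2.2.5. Set no new stopping threshold, so that the CI still judges what is unacceptable.

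The cost is 24 × 4 = 96 assays for the planned completers, up to 30 × 4 = 120 if all patients attend every draw, plus a short amendment. No extra visit or venepuncture is needed. The downside is that incidental raised values will need CI review, and a few could prompt a drug stop in a pilot that plans for 12 completers per arm.

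Assaying the stored day 35 serum later could supply a safety record but would not inform dosing, so it is only a fallback.
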